### 6.3 Sample Size and Accrual

The baseline survey showed that the prevalence of nasopharyngeal carriage with pneumococci of the seven valent vaccine serotype was about 40% in infants up to the age of 2.5 months (the age when the first dose of pneumococcal conjugate vaccine will be given) and 30% in those aged 30 months or more. The coefficient of variation between villages was 0.3. Based on these assumptions and assuming that 50 subjects are studied in each village the trial will have over 90% power with a type 1 error of 5% to detect a 50% reduction in the overall prevalence of pneumococci of vaccine serotype in those over the age of 30 months (prevalence 30% to 15%) and a similar power to detect a 50% reduction in the colonisation of infants with pneumococci of vaccine type before the age of 2 months (prevalence reduced from 40% to 20%). The prevalence of type 1 and type 5 carriage was very low in the initial survey so the study is not specifically powered to detect an increase in carriage with pneumococci of these serotypes but it would detect this if the effect was marked.

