| Phase:                                   | IV                                                                                                                                                                                                                                                                                                                                                                                                                                                                                                                                                            |
| Population:                              | 
Approximately 6000 residents of 21 Gambian villages for vaccination
 
Subsamples of 1250 subjects for evaluation antigenic and molecular characteristics of pneumococci with a subsample of 200 for 5ml blood specimen and saliva.
 
All children born during the study period
 
Subsample of 430 subjects for longitudinal substudy
                                                                                                                                                                                                    |
| Number of Sites:                         | 
Sibanor villages
 
MRC Labs, Fajara, The Gambia
                                                                                                                                                                                                                                                                                                                                                                                                                                                                                                   |
| Study Duration:                          | 36 months (June 2006 until May 2009)                                                                                                                                                                                                                                                                                                                                                                                                                                                                                                                          |

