### 6.2 Outcomes of interest

#### 6.21 Impact on carriage

- (a) Differences in the prevalence of nasopharyngeal carriage of pneumococci of vaccine or of non-vaccine serotype in study villages after vaccination in the cross-sectional samples. Differences in the prevalence of carriage with serotype 1 and serotype 5 pneumococci will be of particular importance.
- (b) Acquisition rates of nasopharyngeal carriage in newborns resident in vaccinated or control villages.
- (c) Rate of capsular switching in villages where community wide pneumococcal conjugate vaccination has been introduced, compared to those receiving placebo.

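### The infant power in 6.3 rests on 50 subjects per village, which births cannot supply at assumed rates of 30–50 per 1000 a year, and it is for a prevalence while outcome 6.21(b) is an acquisition rate

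*Combined protocol and SAP*

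**What the plan says.** Section 6.3 makes a single sample-size statement. It works by "assuming that 50 subjects are studied in each village", with between-village variation given as "The coefficient of variation between villages was 0.3" and a type 1 error of 5%. From this it claims over 90% power for 30% v 15% in those over 30 months, and "a similar power to detect a 50% reduction in the colonisation of infants with pneumococci of vaccine type before the age of 2 months", that is, 40% v 20%. The 40% comes from the baseline survey, where vaccine-type carriage "was about 40% in infants up to the age of 2.5 months". No separate number of infants, birth rate or expected number of births is given anywhere.

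The Schema describes the population as "Approximately 6000 residents of 21 Gambian villages for vaccination" plus the children born during the study, and gives a 36-month duration with participation of up to 24 months. Sections 1.4 and 4.2.1 (Scheduled follow-up) swab every newborn weekly until the first vaccine dose at 2 months. Section 6.21(b) lists the infant outcome as "Acquisition rates of nasopharyngeal carriage in newborns resident in vaccinated or control villages".

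**The concern.** Fifty per village suits the cross-sectional surveys, which take about 1,250 people from 21 villages, or roughly 60 each. It does not obviously suit newborns, whose number is set by the birth rate and cannot be raised by sampling more. If the births do not come, the infant claim of similar power has no sample behind it.

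The second difficulty is the quantity. The claim concerns the proportion carrying vaccine-type pneumococci, with a control value read from a survey. The listed outcome is the rate at which carriage is acquired under weekly swabbing from birth. A rate has its own control value and its own variation between villages, and 6.3 gives neither. A reader would take this newborn outcome to be powered at over 90% when the plan has not shown it.

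**Working it through.** **Inputs.** From 6.3: 40% v 20% in infants, 30% v 15% in those over 30 months, m = 50 per village, k = 0.3, alpha 5% (taken as two-sided; the plan does not say). From 1.4: 10 v 11 villages. Which group has 11 is not stated, so both cases are shown. From the Schema: about 6000 residents, 36 months. From 1.4: 24 months of follow-up. *Assumed, not in the documents:* 30–50 births per 1000 residents per year.

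**Formula** (Hayes–Bennett, unmatched clusters). Variance of a village prevalence: v = p(1−p)/m + k²p². SE² = v₀/(c₀−1) + v₁/(c₁−1), with one village per arm deducted as the usual small-sample correction. Power = Φ(|p₀−p₁|/SE − 1.96).

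**Step 1: reproduce the plan's figure (m = 50).**
- Infants: v₀ = 0.24/50 + 0.09×0.16 = 0.0192; v₁ = 0.16/50 + 0.09×0.04 = 0.0068.
- With 11 control villages, SE = √(0.0192/10 + 0.0068/9) = 0.0517, so z = 0.2/0.0517 − 1.96 = 1.91 and power is 97.2%. With 10 control villages it is 96.5%.
- Over 30 months: v₀ = 0.0123, v₁ = 0.004575; power 94.9% or 94.0%.

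Both claims of over 90% follow from the plan's own inputs.

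**Step 2: can births supply m = 50?**
- Needed: 50 × 21 = 1050 births.
- Over 24 months: 1050/(6000 × 2) = 87.5 per 1000 per year.
- Over 36 months: 1050/(6000 × 3) = 58.3 per 1000 per year.

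Both lie above the whole assumed range.

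**Step 3: power on the births available in 24 months** (equal villages, complete follow-up).

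| Births per 1000/yr (assumed) | Births | Per village | Power, 11 control villages | Power, 10 control villages |
|---|---|---|---|---|
| 30 | 360 | 17.1 | 86.4% | 85.0% |
| 40 | 480 | 22.9 | 91.0% | 89.9% |
| 50 | 600 | 28.6 | 93.6% | 92.6% |

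For example, at 17.1: v₀ = 0.24/17.1 + 0.0144 = 0.0284; v₁ = 0.16/17.1 + 0.0036 = 0.0129; SE = 0.0654; z = 1.10. Power of 90% needs about 22–23 infants per village. A birth window covering all 36 months, an upper bound, gives 540–900 births, 26–43 per village, and about 91–96%.

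**Step 4: what moves the figure** (11 control villages).
- *Unequal villages.* With an assumed coefficient of variation of village size of 0.4–0.6, an unweighted village-level analysis and the harmonic mean of m, power is 76–83% at a mean of 17, 84–89% at 23 and 88–92% at 29.
- *Losses* act through m. Fourteen analysed infants per village gives 82%.
- *A larger k in newborns.* At k = 0.4, power is 75–83% for 17–29 infants, and only 88% even at 50.

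**Step 5: the listed outcome.** A rate r has village variance r/y + k²r², where y is the infant-time at risk. The plan supplies no r and no k for it. As an illustration only, suppose the rate of first acquisition is halved, k is again 0.3, there are 10 control villages, and cumulative acquisition by 2 months in control villages is an assumed 40%, 60% or 80%. Power is then 76%, 86% or 91% at 17 infants per village, and 88%, 93% or 96% at 29. The answer depends heavily on a planning value that the plan omits.

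**The case against.** The plan never says 50 infants. It says subjects, and then claims similar power. Its arithmetic is right for its inputs. Between-village variation dominates: at m = 50 the k² term is 0.0144 of the 0.0192 control-arm variance, so cutting m by half or more costs little. At 40 and 50 births per 1000 a year, power is about 90% or better even on 24 months of births, and a longer birth window would help. All of this stands, and it limits the size of the problem. It does not supply the missing infant number, since 50 is the only cluster size in the section and the infant claim is drawn from it.

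A reader might infer that the infant comparison is badly underpowered. The documents do not support that. On the plan's own effect size and k, the shortfall is a few points to about 12. Much lower values need added assumptions about village sizes, losses, k or effect.

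A reader might also infer that infant prevalence will not be analysed at all. That goes too far. The second objective in section 2.0 covers prevalence as well as acquisition, and weekly swabs yield both. The defect is narrower: 6.21(b) names acquisition alone for newborns, and 6.3 powers something else.

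**Conclusion.** The point holds in a limited form. The cluster size behind the infant power is out of reach at any assumed birth rate from 30 to 50 per 1000 per year, over 24 months and even over 36. Prevalence power on 24-month births is about 85–94% rather than 97%. The claim of over 90% is therefore not assured. It fails toward the low end of the assumed birth rates, and by more if villages differ in size or infants are lost. These figures assume 40% v 20%, k = 0.3 and 10 v 11 villages; the birth rate is the one input from outside the documents.

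The mismatch of quantities needs no assumption. The 40%, the 20% and k = 0.3 describe a prevalence and do not carry over to an acquisition rate, so no power has been stated for 6.21(b). That outcome also does not say whether it means vaccine-type or any pneumococci.

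**What to change.** - In 6.3, replace 50 per village for infants with the expected births per village, using the study census birth rate and a stated birth window. Restate the infant prevalence power, which is about 85–94% on 24-month births at the assumed rates, and allow for unequal villages and losses.
- Name one infant estimand so that 6.3 and 6.21(b) agree: either vaccine-type acquisitions per infant-week at risk to 2 months, or vaccine-type prevalence at a fixed age. Compare it at village level.
- If acquisition is chosen, recompute power from a planning rate and a between-village variation for that rate. The prevalence figure cannot stand in for it.
- Reconcile the ages within 6.3: the 40% refers to infants up to 2.5 months, which 6.3 ties to the first dose, while the claimed reduction is before 2 months and sections 1.4 and 4.2.1 give the first dose at 2 months.

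Cost: wording, one recalculation and a slightly less favourable stated power. No extra infants or swabs.

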### 6.4 Monitoring and Analysis

The MRC Clinical Trials monitor will be responsible for monitoring the trial. This will include site visits to confirming the existence of the appropriate documents in the regulatory folder and of source documents for all required data. She will also assess the accuracy and

completeness of the CRF entries and other records against each other and their consistency with the source documents.

*The data manager will be responsible for data entry, data cleaning and for initial analysis of the results. The main analyses will be descriptive and comparative.*

## 7.0 HUMAN SUBJECTS

### 7.1 Institutional Review Board (IRB) Review and Informed Consent

Approval for the study has been given by the joint Gambia government/MRC ethics committee. Written informed consent will be obtained from the subject (or parent, legal guardian, or person with power of attorney for subjects who cannot consent for themselves, such as, those below the legal age). The subject's assent will also be obtained if he or she is able to understand the nature, significance and risks associated with the study. The informed consent will describe the purpose of the study, the procedures to be followed, and the risks and benefits of participation. A copy of the consent form will be given to the subject (or parent or legal guardian).

### 7.2 Subject Confidentiality

All records will be kept in a secure place. All data on computer files will have restricted access. Clinical information will not be released without written permission of the subject, except as necessary for monitoring.

### 7.3 Data and Safety Management Board (DSMB)

A data and safety management board has been constituted for the trial and a schedule for meetings will be agreed to. DSMB includes the following people: [name] (Kilifi, Kenya), [name] (Banjul), [name] (Oxford University) and [name] (London School of Hygiene and Tropical Medicine). A clinical safety monitor will be selected and a programme of trial monitoring will be set up for the trial.

### 7.4 Study Discontinuation

The MRC SCC or the joint Gambian government/MRC ethics committee may discontinue the study after the appropriate recommendation by DSMB.

## 8.0 PLANS FOR DISTRIBUTION OF RESEARCH FINDINGS TO STUDY COMMUNITY

Written annual progress reports of the trial will be produced. At the end of the study, a research report of the methods, detailed results, and brief conclusions will be prepared for distribution to the collaborators. A simplified lay document will be made available to study subjects.

## 9.0 BIOHAZARD CONTAINMENT

As the transmission of HIV and other blood-borne pathogens can occur through contact with contaminated needles, blood, and blood products, appropriate blood and secretion precautions will be employed by all personnel in the drawing of blood and shipping and handling of all specimens for this study, according to the MRC safety manual.

## **Appendices**

### **GAMBIAN COMMUNITY PNEUMOCOCCAL CONJUGATE VACCINE TRIAL- CONSENT PROCEDURE**

1. The project investigators will hold discussions with village heads and elders in villages in the study area to determine if they are interested in participating in the study.
2. If village elders are encouraging, village meetings will be held, which will be open to the whole community. At these meetings the nature of the trial and what it involves for the village will be discussed. General consent for a village to join the trial will be sought at the meeting and if this is given, this will be documented formally.
3. In villages that agree to join the trial, the head of each compound will be visited. The nature of the trial and what this will involve for his household will be explained by a trained field assistant and an opportunity will be given to ask questions. If the compound head wants his household to join the trial, information sheets will be provided and explained after which he/she will be asked to sign a consent form (Consent form 1).
4. At the time of vaccination, study individuals or the guardians of small children will be asked for their consent to vaccination. The fact that the respondent gave permission will be recorded on a special form by the field assistant who asks for permission
5. Whenever a nasopharyngeal swab or blood sample is collected, the study subject or guardian will be reminded that they are under no obligation to provide the sample and that they can withdraw from the study at any time. If permission is given this will be noted by the field assistant on a form.
6. Subjects asked to join the longitudinal study in which nasopharyngeal swabs will be collected will be asked to sign a separate consent form (Consent form 2)
